**Figure 1 F1:**
[figure not shown]
Flow of the early and delayed implementation support groups through the study.

### Economic evaluation overview

This economic evaluation will be conducted from the healthcare, aged care and disability care funders’ perspective. All costs will be valued in 2024 $A. Within-trial cost-effectiveness and cost-utility analysis will be conducted as part of the *PROMOTE-PA* study, to determine the incremental costs and incremental health outcomes of the implementation strategies for PA promotion compared with usual care. Data linkage will be used to determine and compare levels of healthcare utilisation among patients of health professionals receiving support for PA promotion compared with usual care over 2 years. Decision-analytical modelling will be used to determine the incremental costs and health outcomes with an extended time horizon of 2 years. The economic evaluation will be reported according to the Consolidated Health Economic Evaluation Reporting Standards.^12^ A statistical analysis plan for the within-trial and modelled analyses will be written and signed by the study authors prior to the commencement of data analysis.

### Within-trial analysis

The time horizon for the within-trial analysis is 6 months, representing the length of follow-up for patient participants in the trial. Costs and health outcomes will not be discounted as the time horizon is less than 12 months. The analysis will follow an intention-to-treat approach.

#### Measurement and valuation of health outcomes (within-trial analysis)

Intervention (patient-level) and implementation (health professional-level) outcomes will be used in this economic evaluation. The patient-level outcomes used will be the self-reported time spent in moderate-to-vigorous PA (MVPA) over the past week (reported in hours/week using a modified version of the PA vital sign)^13^ and QALYs (derived from the EuroQol 5-dimensions 5 level-version (EQ-5D-5L) or EuroQol 5-dimensions youth version (EQ-5D-Y)).^14 15^

The effectiveness outcome measure for the within-trial cost-effectiveness analysis will be the difference in proportion of participants achieving 150 min of MVPA per week in the intervention group, compared with the control group at 6 months.

The effectiveness outcome measure for the within-trial cost-utility analysis will be QALYs gained in the intervention group, compared with the control group over 6 months. Utility-based quality of life will be measured using the EQ-5D-5L^15^ in adults and the EQ-5D-Y^14^ in children and adolescents (aged 5–17 years). The EQ-5D-5L measure includes five dimensions: mobility, self-care, usual activities, pain/discomfort and anxiety/depression. Each item is rated on a five-level scale, ranging from no problems to extreme problems within each dimension. Australian scoring algorithms will be used to calculate a health utility score based on the EQ-5D-5L.^16^ The EQ-5D-Y includes the same five dimensions, reworded for relevance to children, but is instead scored on a 3-level scale. As an Australian scoring algorithm for the EQ-5D-Y has not yet been published, a valuation from a country with a similar population will be used (ie, the Netherlands).^17^ The health utility scores fall on a scale of 0.0 (dead) to 1.0 (perfect health). In the instance that a participant passes away during the trial, they will be assigned a health utility score of 0 from that point forth. Health utility scores at baseline and 3-month and 6-month follow-ups will be used to calculate QALYs using the following formula:

QALYs=healthutilityscore×timespentinhealthstate

The health professional-level outcome (secondary question) used will relate to the level of PA promoted by health professionals, captured using self-reported study-specific surveys including questions about health professionals’ PA promotion behaviours at baseline and 6-month follow-up. The effectiveness outcome measure for this within-trial cost-effectiveness analysis will be the change in PA promotion in the intervention group compared with the control group at 6 months.

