#### Analysis and sensitivity analysis (within-trial analysis)

Data analysis will be conducted using Stata V.16 (Stata Corp, College Station, Texas). The within-trial cost-effectiveness and cost-utility analyses will include total costs and effects over the 6-month trial follow-up period.

Incremental cost-effectiveness ratios (ICERs) will be calculated to determine the additional costs required to achieve the additional health outcomes associated with the implementation strategy. This will be measured in terms of gains in patient PA participation and health professional PA promotion (cost-effectiveness analysis) and QALYs (cost-utility analysis). The following formula will be used to calculate the ICER:

$$ICER=\frac{Implementation\;support\;costs\;-Usual\;care\;cost\;costs}{Implementation\;support\;effects-Usual\;care\;effects}$$

Clustering will be considered to take into account similarity within and difference between clusters when calculating the incremental costs and health outcomes.^19^ To examine uncertainty around the ICERs for PA participation, QALYs and PA promotion, bootstrapping with at least 1000 iterations will be used to estimate a distribution around costs and health outcomes, with results to be plotted on a cost-effectiveness plane. Bootstrapping will also be used to estimate 95% CIs around the ICERs. A cost-effectiveness acceptability curve will be generated to explore the probability of the intervention being cost-effective at different willingness-to-pay thresholds. To assess the robustness of results, one-way and multiway sensitivity analyses will be undertaken to see how study results change when using different assumptions and parameters (eg, under-reporting or over-reporting of self-reported PA, unit prices used for valuing resource use, methods for handling missing data).^20 21^ Cost and effectiveness outcomes will be presented as outlined in table 2.

**Table 2 T2:** Cost and effectiveness outcomes and ICERs in base case, sensitivity and subgroup analysis

	Intervention	Usual care	Mean difference (bootstrapped 95% CI)
Base case analysis			
Total cost per participant ($A) (mean, SD)			
Total QALYs (mean, SD)			
ICER for QALYs			
Proportion of participants meeting MVPA guidelines (n, %)			
ICER for MVPA			
Scenario analysis—no extra staff cost			
Total cost per participant ($A)			
Total QALYs (mean, SD)			
ICER for QALYs			
Proportion of participants meeting MVPA guidelines (n, %)			
ICER for MVPA			
Sensitivity analysis			

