We acknowledge that there are some limitations to our planned economic evaluation. Given the highly tailored nature of the implementation support provided to clinical teams in the *PROMOTE-PA* trial, it is likely that the level of support, and therefore associated costs, may vary significantly across teams. This may also have implications for generalisability across clinical teams in different hospitals or local health districts operating within a different clinical context.

The primary outcome used for the trial-based cost-effectiveness component of this economic analysis is a self-reported measure of PA participation. While a sufficiently valid and reliable tool will be used, there is a risk of participants overestimating PA participation, which could impact the resulting ICER.

The primary cost-effectiveness and cost-utility analyses are being conducted from the perspective of the healthcare, aged care and disability care funder. As such, information is not being collected on patient out-of-pocket costs (eg, healthcare-related costs, equipment purchased to support an increase in PA, costs associated with signing up to gyms and sports clubs) or costs related to productivity losses. Adopting a broader perspective, such as a societal perspective, would provide a more complete indication of the economic impact of the intervention. However, given limited resources and considering the likely role of these funders in future implementation, adopting the healthcare, aged care and disability care funder perspectives is the most feasible and relevant in this case.

In this pragmatic trial, it is not feasible for health professionals to be blinded to group allocation at the time of patient recruitment. This presents a risk for potential differential recruitment. We will report baseline patient characteristics, including age, medical conditions and PA levels according to group allocation to look for evidence of differential recruitment impacts and aid in the interpretation of our findings.

Through conducting a cost-effectiveness and cost-utility analysis as well as providing detailed information around implementation, intervention and healthcare utilisation costs, this economic evaluation will contribute to increasing the knowledge base around economic evaluations of supported implementation of healthcare interventions. Understanding the cost-effectiveness and cost-utility of the implementation strategies will also inform the potential for future scale-up.

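### The article answers its own recruitment-bias risk only with a baseline table; the incremental QALY and MVPA contrasts should be specified as adjusted for baseline

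*Protocol article*

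**What the plan says.** **Effect measures.** The Protocol article, section Measurement and valuation of health outcomes (within-trial analysis), sets the cost-effectiveness outcome at the 6-month visit: it "will be the difference in proportion of participants achieving 150 min of MVPA per week in the intervention group, compared with the control group at" that visit. The cost-utility outcome "will be QALYs gained in the intervention group, compared with the control group over 6 months". On its construction: "Health utility scores at baseline and 3-month and 6-month follow-ups will be used to calculate QALYs".

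**Increments.** Analysis and sensitivity analysis (within-trial analysis) defines the ICER as the difference in costs over the difference in effects. The one consideration it names for the increments is: "Clustering will be considered to take into account similarity within and difference between clusters when calculating the incremental costs and health outcomes". Table 2 has a column for each arm and a third headed "Mean difference (bootstrapped 95% CI"). The examples of sensitivity analyses are "under-reporting or over-reporting of self-reported PA, unit prices used for valuing resource use, methods for handling missing data". Baseline adjustment is not among them.

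**Recruitment bias.** The Discussion says professionals cannot be blinded to allocation when patients are recruited, and continues: "This presents a risk for potential differential recruitment. We will report baseline patient characteristics". The characteristics it lists are age, medical conditions and activity levels. Their stated use is to look for signs of differential recruitment and to help interpretation.

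**SAP.** Economic evaluation overview says a statistical analysis plan will be written and signed before data analysis begins. It is not shown.

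**The concern.** The article names a threat to comparability and pairs it with a response that can detect the problem but cannot change the estimate. A baseline table tells the reader that the arms differ. The ICER is still computed from whatever contrast was specified, and the only feature specified for that contrast is clustering.

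The QALY is especially exposed because baseline utility is one of its components. A difference that existed before any intervention is counted as a QALY gain or loss, even if it vanishes by 3 months. Baseline utility is also not among the characteristics listed for reporting. The MVPA contrast is taken at 6 months only, so baseline imbalance reaches it through persistence of activity habits. By comparison, the secondary professional-level outcome is defined as a change and uses baseline and 6-month surveys.

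Selection is not needed for imbalance to arise, since 30 clusters leave room for chance. Age mix adds another route. Clusters may come from a children's health network, and patients aged 5 to 17 are scored with a different instrument (EQ-5D-Y) and a Dutch tariff. An uneven split of children and adults between arms could therefore shift mean utility by itself.

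At stake are both primary ICERs. A bootstrap around an unadjusted difference resamples the bias along with the data and does not remove it.

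**Working it through.** The article gives no utility SD, correlation, ICC, expected effect or expected cost, so it has no figure of its own to reproduce. The following sizes the mechanism.

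**From the article:** utility at 0, 3 and 6 months; 30 clusters; 720 patients, so 720/30 = 24 per cluster.

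**Assumed:** trapezoid area under the curve; 15 clusters per arm; carry-over r (the share of a baseline difference still present at follow-up); utility SD 0.15 to 0.25; ICC 0.01 to 0.10; illustrative costs and effects.

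**1. Weights.** With two intervals of 0.25 years, QALY = 0.125·u0 + 0.25·u3 + 0.125·u6.

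**2. Bias of an unadjusted QALY difference.** If the arms differ by d at baseline and by r·d at follow-up in the absence of any effect, then bias = d(0.125 + 0.375r).
- Per d = 0.01: r = 0.5 gives 0.0031; r = 0.8 gives 0.01 × 0.425 = 0.0043.
- Limits per d = 0.01: r = 0 gives 0.0013; r = 1 gives 0.0050.
- For d = 0.03: r = 0 gives 0.0038; r = 0.5 gives 0.0094; r = 0.7 gives 0.0116; r = 1 gives 0.0150.

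**3. Imbalance by chance alone.** SE(d) = SD × √[(2/360)(1 + 23·ICC)].
- SD 0.15, ICC 0.01: 0.012.
- SD 0.25, ICC 0.10: 0.034.
- At r = 0.7 the multiplier is 0.125 + 0.375 × 0.7 = 0.3875, so a one-SE imbalance gives a bias of 0.005 to 0.013 QALY.

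**4. Effect on the ICER (illustration).** Take an incremental cost of $A300 and a true gain of 0.010 QALY, so the true ICER is $A30,000.
- Bias +0.0116: 300/0.0216 = about $A13,900.
- Bias −0.0116: the QALY difference becomes −0.0016, a change of sign.

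**5. MVPA.** A 5-point baseline imbalance with 30% to 70% carry-over gives 1.5 to 3.5 points of bias. At $A300 and a true 10-point difference, the ICER moves from $A3,000 to 300/0.115 = about $A2,610, or to 300/0.135 = about $A2,220.

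**6. Precision.** With equal variances and a common correlation r between visits, R² of the QALY on baseline utility = (0.125 + 0.375r)² / (0.09375 + 0.15625r).
- r = 0.5: 0.0977/0.1719 = 0.568.
- r = 0.8: 0.1806/0.2188 = 0.826.

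Adjustment thus removes 57% to 83% of patient-level QALY variance, and the patient-level SE falls by 1 − √(1 − R²) = 34% to 58%. These figures are before cluster effects. Part of the R² is built in, because baseline utility is inside the QALY.

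**The case against.** The strongest objection is that a reader might infer that the article commits to raw, unadjusted differences. It does not. No sentence says raw or unadjusted, the outcome definitions fit an adjusted difference equally well, and the ICER formula is the generic one. The Table 2 heading leaves the matter open, and the sensitivity analyses are given only as examples. Covariates are a routine SAP item, and an SAP is promised. All of this stands, and it limits the point to what the article states and fails to commit to.

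It does not dispose of the point. The article chose to state its response to recruitment bias, and that response is descriptive only. It also chose to name what would be considered when calculating the increments, and named clustering alone. Followed as written, this gives a weaker estimate than one using baseline values that are already collected.

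Other parts of the objection also stand:
- The Discussion names a risk of differential recruitment. A reader might take this as an expectation, but the text does not go that far.
- Imbalance does not pass whole into the ICER. The share depends on r, which is assumed.
- The size of a plausible 6-month QALY effect cannot be taken from the article, so the bias cannot be ranked against it.
- Selection on unmeasured factors, such as motivation, would survive adjustment.
- The precision gain is at patient level. With 30 clusters, between-cluster variance may limit it.
- Adjusting costs for pre-baseline linked costs has no support in the article, which does not say that such data will be extracted.

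**Conclusion.** The point holds in limited form. The article acknowledges a recruitment-bias risk, answers it with a baseline table, and names no baseline adjustment for either primary contrast. If the increments were computed that way, each 0.01 of baseline utility imbalance would add or subtract about 0.003 to 0.004 QALY, assuming trapezoid QALYs and r of 0.5 to 0.8. Chance imbalance of one SE could give 0.005 to 0.013 QALY under the assumed SD, ICC and r = 0.7. The MVPA contrast is exposed in the same way, in part.

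The mechanism is firm; its size rests on assumed inputs. Whether the final analysis will be unadjusted is not known, because the SAP is not shown. The severity is therefore below must-fix.

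**What to change.** State in the SAP, and in any update of the article, that:
- incremental QALYs are estimated with adjustment for baseline utility, and the MVPA contrast with adjustment for baseline MVPA;
- both models include child/adult age group, since instrument and tariff differ;
- the adjustment sits within the cluster-adjusted model and is refitted in every bootstrap replicate;
- the adjusted differences enter the ICERs and the difference column of Table 2;
- the unadjusted difference is kept as a sensitivity analysis.

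Add baseline utility to the characteristics reported by arm, and say plainly that adjustment addresses measured imbalance only.

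The cost is a few lines of text and slightly more programming. Baseline utility is already collected, and baseline activity levels are already to be reported by arm, so no new data are needed.

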### *PROMOTE-PA *trial

#### Study population

Patient participants will be 720 individuals aged 5 years and above living in the community who are receiving outpatient care from health professionals (n=30 clusters) at one of the multiple participating local health districts, a specialty children’s health network or a private clinic in New South Wales, Australia.

Study recruitment commenced in February 2024 and is expected to finish by December 2025. Participant follow-up is expected to be completed in December 2026.

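### The base-case QALY pools adults on Australian EQ-5D-5L values with children on Dutch EQ-5D-Y values, and the only stated separation is an exploratory paediatric subgroup

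*Protocol article*

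**What the plan says.** The Study population section states: "Patient participants will be 720 individuals aged 5 years and above living in the community". The sites include "a specialty children’s health network or a private clinic in New South Wales, Australia". The number of children, and of clusters that treat children, is not given.

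The section on measurement and valuation of health outcomes (within-trial analysis) treats QALYs as one patient-level outcome obtained from either of two instruments. For adults, "Australian scoring algorithms will be used to calculate a health utility score based on the EQ-5D-5L". The EQ-5D-Y is used "in children and adolescents (aged 5–17 years"); it has three levels per dimension instead of five and reworded items. Because no Australian algorithm for it had been published, "a valuation from a country with a similar population will be used (ie, the Netherlands"). The QALY formula is "QALYs=healthutilityscore×timespentinhealthstate", with utility taken at baseline, 3 and 6 months.

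Table 2 has a single base-case row, "Total QALYs (mean, SD"), for each arm, followed by a single ICER for QALYs. The text under Table 2 plans exploratory subgroup analyses, one of them for ages 5–17. No adult-only analysis is named. The sensitivity analyses given as examples concern self-reported activity, unit prices and missing data. The Modelled economic analysis section carries the same outcome forward to 2 years.

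**The concern.** A utility from a five-level form with Australian weights and one from a three-level form with Dutch weights are not the same unit. The same health state, or the same change in health, can receive a different value depending on the form completed, and the form is decided by age. Pooling has two consequences.

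First, if the arms differ in their share of children, any difference in mean utility between the two groups enters the unadjusted QALY difference. With 30 randomised units, such an imbalance can arise by chance. The Discussion gives a second route: health professionals know their allocation when patients are recruited, and the article acknowledges a risk of differential recruitment. That route could be systematic.

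Second, even with balanced arms, the pooled ICER averages changes measured on two scales, and part of it rests on Dutch preferences. The perspective is that of Australian funders, yet no stated cost-utility result rests on Australian values alone.

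**Working it through.** The article gives no QALY difference, utility gap or paediatric share, so there is no figure to reproduce. The check asks how large the effect could be.

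**Inputs from the article:** 720 patients, 30 clusters, 6 months = 0.5 year. Average cluster size is 720/30 = 24.

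**Assumptions:** 15 clusters and 360 patients per arm; a difference of 13.3 percentage points in the share of children; a mean utility gap between the two groups of 0.02 to 0.10, constant over follow-up. The imbalance corresponds to 48 children (48/360 = 0.133), the content of two average clusters (2 × 24 = 48). It does not require wholly paediatric clusters.

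**Formula:** shift in the unadjusted QALY difference = difference in share × utility gap × 0.5 year.

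| Assumed gap | Calculation | Shift (QALY) |
|---|---|---|
| 0.02 | 0.133 × 0.02 × 0.5 | 0.0013 |
| 0.05 | 0.133 × 0.05 × 0.5 | 0.0033 |
| 0.10 | 0.133 × 0.10 × 0.5 | 0.0067 |

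The sign depends on which arm has more children and which group scores higher; neither is known.

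**Scale.** A utility gain rising linearly from 0 to 0.03 over 6 months is worth 0.03 × 0.5 × 0.5 = 0.0075 QALY. For an assumed true gain of 0.010 QALY at an incremental cost of A$300, the ICER is 300/0.010 = A$30,000.
- A shift of ±0.0013 moves it to 300/0.0113 ≈ A$26,500 or 300/0.0087 ≈ A$34,500.
- A shift of ±0.0067 moves it to 300/0.0167 ≈ A$18,000 or 300/0.0033 ≈ A$91,000.

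The gain and the cost are illustrative only.

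**Does the usual adjustment deal with it?** A simulation with no true effect used 2,000 runs, 30 clusters of 24, six paediatric clusters split 4:2, a within-cluster utility SD of 0.18, within-person correlation 0.6 and a between-cluster SD of 0.03. Mean QALY differences were:

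| Gap | Unadjusted | Adjusted for baseline utility | Adjusted for age/instrument group |
|---|---|---|---|
| 0.05 | 0.0032 | 0.0010 | about 0 |
| 0.10 | 0.0067 | 0.0019 | about 0 |

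Under these assumptions baseline-utility adjustment removes about 70% of the shift and leaves about 30%. A term for age/instrument group removes essentially all of it, with or without baseline utility.

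**The case against.** The strongest reply is that the article does not fix an unadjusted comparison. It describes no QALY regression, says only that clustering will be taken into account, and promises a signed analysis plan before analysis. Randomisation detail is left to the separate trial protocol. A single row in Table 2 is compatible with an adjusted or stratified estimate. This stands: a reader might infer that the base case has no term for instrument and that randomisation was unstratified, but the article is merely silent on both, and such detail commonly sits elsewhere.

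A reader might also infer that an uneven split is likely because children's services form whole clusters. The article lists a children's network among the sites but does not say how clusters divide by age or how many treat children. Any probability of imbalance therefore rests on invented inputs, and none is claimed here.

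Nor can the whole gap be put down to scoring. Children and adults may truly differ in health, and that difference would appear under a single instrument too.

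Chance imbalance under randomisation adds variance rather than systematic bias, and a bootstrap that respects clusters would partly reflect it. With the simulation's SD and correlation, the QALY SD is about 0.078, so the standard error with 360 per arm is 0.078 × √(2/360) ≈ 0.006 before any design effect. The shifts above run from about a fifth of a standard error to a little over one. They would still move the point estimate in the trial as realised.

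Finally, the Dutch value set is disclosed and justified, the list of sensitivity analyses is open-ended, and the Discussion commits to reporting age by arm, which would reveal an imbalance. Revealing it does not correct the QALY estimate, and none of these safeguards supplies a result on one value set.

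**Conclusion.** The point holds as a limited one. The article fixes a single base-case QALY and ICER across two instruments and two national value sets, and the only separation it states is an exploratory paediatric subgroup. The absence of any stated result resting wholly on Australian values does not depend on imbalance.

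The numerical effect is conditional: about 0.001 to 0.007 QALY over 6 months for a 13-point imbalance and a gap of 0.02 to 0.10. It assumes that nothing in the trial protocol or the analysis plan already balances or adjusts for age group. The documents do not show that an imbalance will occur, that the base case will be biased, or how much of any gap is due to scoring. This is an inexpensive improvement to make before the analysis plan is signed, not an error that invalidates the evaluation.

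**What to change.** In the analysis plan:

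1. Estimate incremental QALYs separately in adults (EQ-5D-5L) and ages 5–17 (EQ-5D-Y), and combine the two differences with weights fixed in advance, such as each group's share of the whole sample. Alternatively, adjust the QALY model for age/instrument group together with baseline utility. Apply the same estimator within each bootstrap replicate.
2. Add to Table 2 an adult-only cost-utility result on the Australian value set, using the costs of the same participants, beside the pooled base case and the planned paediatric subgroup. State how implementation costs are apportioned if a cluster recruits both age groups.
3. State in the text that the pooled QALY combines two instruments and two value sets.

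If the trial protocol already stratifies on paediatric status, say so and keep items 1 and 2; balance does not make the two scales equivalent.

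The cost is analysis-plan wording and an extra block of rows in Table 2. Age and instrument are already recorded, so no new data are needed. The adult-only result will be somewhat less precise than the pooled one, and a small paediatric group would make its own estimate imprecise.

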## Introduction

 Physical activity (PA) has a multitude of health benefits, including reducing mortality and aiding in the prevention and management of chronic diseases such as cardiovascular disease, diabetes and cancer.^1^ However, physical inactivity remains a pressing global health issue, leading to 5.3 million avoidable deaths annually.^2^ To address this issue, the evaluation and widespread implementation of suitable PA interventions are urgently needed.

International organisations such as the WHO and International Society for Physical Activity and Health have advocated for PA promotion to be integrated into healthcare settings, with health professionals holding a valuable opportunity to promote PA to a large group of people across the lifespan.^3 4^ Health professionals themselves have indicated a strong interest in supporting their patients to be more active.^5 6^ However, this is limited by a number of reported barriers to providing this support, such as limited skills in facilitating behaviour change, a lack of suitable local PA options and limited knowledge of and trust in available community-based PA programmes.^5 7^

In this context, the *Promotion of PA by Health Professionals (PROMOTE-PA)* trial is a hybrid type 1 effectiveness-implementation cluster randomised trial that has been designed to investigate the effect of PA promotion by health professionals (n=30 clusters) with support from a research team on PA levels among patients (n=720) receiving care in outpatient or community settings.^8^ In addition to determining the effectiveness of the implementation strategies, decision makers will likely also be interested in whether the intervention represents value for money when considering implementation.^9 10^

Therefore, the objective of this study is to conduct an economic evaluation of PA promotion supported by implementation strategies compared with usual care of patients, with a view to inform implementation of similar programmes in other healthcare settings in the future.

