### Economic questions

Primary:

From the perspective of healthcare, aged care and disability care funders, what is the cost-effectiveness and cost-utility (incremental costs and health outcomes in terms of PA and quality-adjusted life years (QALYs)) of PA promotion by health professionals with support from the research team compared with usual care over 6 months?

Secondary:

From the perspective of the healthcare funder, what is the cost-effectiveness (incremental costs and health outcomes in terms of PA promotion by health professionals (implementation outcome)) of PA promotion by health professionals with support from the research team compared with usual care over 6 months?What is the level of healthcare utilisation among patients of health professionals receiving support for PA promotion compared with usual care over 2 years?From the perspective of healthcare, aged care and disability care funders, what is the cost-effectiveness and cost-utility (incremental costs and health outcomes in terms of PA and QALYs) of PA promotion by health professionals with support from the research team compared with usual care over 2 years?

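### The professional-level effect is defined as a difference in change from baseline with no baseline adjustment named; adjusting for the baseline survey already collected would usually be somewhat more precise

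*Protocol article*

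**What the plan says.** In the protocol article, the section on measurement and valuation of health outcomes (within-trial analysis) says that study-specific surveys capture "PA promotion behaviours at baseline and 6-month follow-up". It then sets the effectiveness measure for the secondary question as "the change in PA promotion in the intervention group compared with the control group at 6 months". In the same section the patient MVPA effect is worded differently, as a between-arm difference in the proportion reaching the threshold at 6 months, with no reference to change.

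Under Economic questions, the outcome belongs to a secondary question, framed as "health outcomes in terms of PA promotion by health professionals (implementation outcome" and costed over 6 months. The section on analysis and sensitivity analysis (within-trial) puts it into an ICER, whose effects are "gains in patient PA participation and health professional PA promotion (cost-effectiveness analysis" and, for the cost-utility analysis, QALYs. The denominator is the implementation-support effect minus the usual-care effect. On adjustment, that section says only: "Clustering will be considered to take into account similarity within and difference between clusters when calculating the incremental costs and health outcomes". For uncertainty, "bootstrapping with at least 1000 iterations will be used to estimate a distribution around costs and health outcomes". Baseline adjustment of the professional-level outcome is neither stated nor excluded.

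**The concern.** With a survey at both times and an effect worded as change, the natural reading is the mean change in one arm minus the mean change in the other. That contrast subtracts the whole baseline difference, so it fixes the baseline coefficient at 1. The slope that best predicts follow-up from baseline is rho when the two variances are equal, and it is below 1 for any imperfectly repeatable measure. Two things follow. Part of the baseline noise is carried into the estimate, and if the arms happen to differ at baseline, the correction for that difference is too large.

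What is at stake is the denominator of the PA-promotion ICER. Its noise passes into the cost-effectiveness plane and the interval around the ratio. The Discussion says that findings at this level may guide which implementation strategies to adapt or prioritise. The baseline value is already being collected, so the loss is avoidable.

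**Working it through.** The article gives no SD, correlation, effect size or power for this outcome, so there is no stated figure to reproduce. The check compares two estimators over an assumed range of rho.

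**Inputs**
- From the article: 30 clusters ("health professionals (n=30 clusters", Introduction), and a survey at baseline and at 6 months.
- Assumed: 15 clusters per arm (the allocation ratio is not stated in this article); a continuous score with the same SD (sigma) at both times; rho from 0.3 to 0.95. For the 30-unit calculation the unit is the team, so sigma and rho refer to team-level scores.

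**Variance per unit**
- Unadjusted change: 2·sigma²·(1 − rho)
- Baseline-adjusted: sigma²·(1 − rho²)
- Ratio, adjusted to change: (1 − rho²) / [2(1 − rho)] = (1 + rho)/2

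**Cost of estimating the slope with 30 units.** The adjusted variance is inflated by about 1 + 1/(30 − 4) = 1.038. A simulation of 30 independent units, 20,000 runs per rho, includes this cost directly. The interval-width ratio uses the inflation factor and t quantiles on 27 and 28 degrees of freedom.

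**Chance imbalance.** If the arms differ by d SD at baseline, the change-score estimate is expected to be off by −(1 − rho)·d, against the arm that started higher. With 15 teams per arm, the SD of a chance difference in arm means is sqrt(2/15) = 0.37 team-level SD, so d = 0.3 is unremarkable.

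| rho | change, 2(1 − rho) | adjusted, 1 − rho² | ratio, large sample | ratio, 30 units (simulated) | 95% CI width ratio, 30 units | shift at d = 0.3 (SD) |
|---|---|---|---|---|---|---|
| 0.3 | 1.40 | 0.91 | 0.65 | 0.68 | 0.82 | −0.21 |
| 0.5 | 1.00 | 0.75 | 0.75 | 0.78 | 0.88 | −0.15 |
| 0.7 | 0.60 | 0.51 | 0.85 | 0.88 | 0.94 | −0.09 |
| 0.9 | 0.20 | 0.19 | 0.95 | 0.98 | 0.995 | −0.03 |
| 0.95 | 0.10 | 0.0975 | 0.975 | 1.02 | 1.01 | −0.015 |

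The inflation formula puts break-even with 30 units at (1 + rho)/2 × 27/26 = 1, that is rho = 52/27 − 1 = 0.93. Below that adjustment gains; above it the slope costs slightly more than it saves.

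**Averaged over randomisations**, d has mean zero, so the shift averages to zero and the change score is unbiased. The shift and the variance loss are two views of one cost and should not be added together.

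**The case against.** The strongest reply is that the article names an outcome, not a model. Regressing change on arm plus baseline gives exactly the same arm coefficient as regressing the 6-month score on arm plus baseline; only the baseline coefficient differs, by 1. The article also promises, under Economic evaluation overview, a separate analysis plan that is signed before anyone analyses the data. That plan is not shown, and it could include baseline as a covariate without contradicting anything here. This stands, and it limits the weight of the point. It does not remove it: the article defines this effect as a change, names clustering as the only adjustment, and so permits the unadjusted contrast.

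The wording may also be loose. The analysis section speaks of gains for MVPA too, although that effect is defined as a 6-month difference, so that phrase does not corroborate a change-score analysis. The reading rests on the definition itself.

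The formulas assume a continuous score with equal variances. The survey scale is not described and could be binary, ordinal or a count; the principle carries over, the exact ratios do not. Table 2 has no row for a PA-promotion ICER, which fits a secondary role.

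Some stronger readings are tempting but unsupported:
- A reader might infer that only professionals who answer both surveys are analysed. The article does not say so; it states intention-to-treat and lists missing-data methods among its sensitivity analyses.
- A reader might call this the least precise effect in the plan. No SD or number of professionals is given, and the patient outcomes rest on the same 30 clusters.
- A reader might convert the variance ratio into an equivalent number of extra professionals. That fails in a cluster trial, because adding professionals within existing teams does not reduce between-team variance.

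**Conclusion.** The point holds as a minor one. As worded, the professional-level effect is a between-arm difference in change with no baseline adjustment named. Analysed that way, it would be valid on average but usually less precise than it need be, and it would over-correct whatever imbalance this one trial happens to have. Over an assumed rho of 0.3 to 0.9, adjustment lowers the variance by 35% to 5% in large samples and by about 32% to 2% with 30 analysed units, with no gain near rho = 0.95. These figures rest on a continuous score, equal variances, 15 teams per arm and an unknown rho. It would be wrong to conclude that the change score is biased by design, or that the plan has ruled out adjustment. The outcome is secondary, and no sample size or decision threshold in the article depends on it.

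**What to change.** In the analysis plan, or by a clarification to the outcome definition, state that the professional-level effect is the between-arm difference in 6-month PA promotion, adjusted for baseline PA promotion and allowing for clustering by team. Regressing change on arm plus baseline is equivalent, so the change wording can stay if baseline is named as a covariate. If the score is binary or ordinal, use a suitable regression with baseline as covariate. Re-estimate this adjusted difference in each bootstrap replicate, so that the ICER, the plane and the acceptability curve all use it.

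The cost is one sentence. No new data are needed, and the article says the analysis plan will be signed before data analysis starts.
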